Atopy will be assessed using skin prick testing (SPT). Highly standardized ALK allergens will be used including tree, grass and weed pollens, cat, dog, *D. pteronyssinus*, *D. farinae*, cockroach, *Alternaria*, *Cladosporium*, *Aspergillus*, and *Penicillium*. Cow's milk, egg white, soy, wheat and peanut will also be tested. The same batch of each allergen will be used for all subjects. The wheal and flare, at 10 min to histamine and at 15 min for allergens, will be outlined in pen and transferred to paper (hard copy) by adhesive tape. The maximum weal and flare diameters and their mid-point perpendicular responses will be measured. Data will be corrected for any negative control response. Mean responses of both 2mm and 3mm greater than the negative control will be used in analyses, allowing comparison with studies using either of these wheal sizes to indicate a positive response.

*Follow-up post day 21:* After the follow-up visit at 21 days, a research assistant will contact the parents on day 35 by telephone. At this interview we will collect any adverse events and whether a repeat exacerbation has occurred. Specifically, the parent(s) will be asked if their children has been taken to a physician's office, urgent care clinic, or ED for treatment of worsening respiratory symptoms (*Appendix I – Patient Telephone Follow-Up Form day 35*). Follow-up will be either by phone or by email depending on the parent's preference.

**Viral Testing:** Nasopharyngeal swabs will be collected at the time of presentation to the ED and at 21 day follow-up, and tested for wide-range of viruses including human bocavirus, influenza A, influenza B, parainfluenza 1-4, RSV, adenoviruses including H1N1, human metapneumovirus, coronaviruses (OC43, 229E, NL63 and HKU1) and picornaviruses (rhinoviruses and enteroviruses) by utilizing molecular-based procedures.

**Culture independent bacterial profiling:** Nasopharyngeal swabs will be used for culture independent profiling of bacteria (*Appendix K – Details of Culture Independent Bacterial Profiling*). Briefly, total DNA will be prepared from all NP swabs obtained at enrolment and at day 21 follow-up. All samples will be analyzed by 16s rRNA gene amplification and Terminal Restriction Fragment Length Polymorphism (T-RFLP) analysis. Forty of the initial presentation samples will also be analysed by in depth 16S rRNA gene sequencing using Flx Titanium Pyrosequencing to generate >150,000 gene sequences. This 16S rRNA gene library will be used to generate a pediatric nasopharyngeal microbiome database and *in silico* restriction fragment profile for T-RFLP peak identification. Comparison of presentation and post treatment samples will be used to identify specific bacterial responses to azithromycin treatment. We predict that post-treatment samples should have a lower overall bacterial load but will have a T-RFLP profile that reflects the baseline normal microbiota for the nasopharynx. The T-RFLP profiles will also be examined for signatures corresponding to specific pathogens such as *Mycoplasma pneumoniae* and *Chlamydia pneumoniae*. When present, these samples will be further characterized by quantitative PCR. The strategy outlined in Appendix K will capture atypical bacterial and pathogens that elude detection by standard clinical microbiology.

**Medical Chart review:** Each patient's ACH, SCH, or other Alberta hospital medical records will be reviewed at 6 months following enrolment to confirm any visits to an emergency department, admissions to hospital, and document the diagnosis and treatment they received (*Appendix L – Medical Chart Review Form*). A random number of charts will be independently reviewed by both an investigator and a research assistant to establish reliability of data abstraction. Private physicians' offices will also be contacted to confirm the dates and purpose of any visits.

**SABA usage:** As noted previously, the parents will be given a salbutamol MDI fitted with a dose counter (Doser™, Meditracker) to treat their child at discharge from the ED, and then collected at In-Person Follow-up on day 21. The Doser™ has the capability of logging without the user's awareness the number of times the MDI is administered each day for up to 30 days. This will provide an objective count of the number of days an enrolled child receives rescue bronchodilator treatment.

### **Outcome Measurements:**

**Primary Outcome:** - The primary outcome will be the time taken for children to resolve their acute respiratory symptoms (defined as three consecutive days of their child having either no (*green star*) or usual (*yellow star*) respiratory symptoms (*Appendix G – Ordinal Daily Symptom and Drug Dosing Diary*)). If a child at the 21 day follow-up has not resolved their acute symptoms, parents will be given another Nominal Daily Score Diary, and asked to continue to monitor symptoms for another 21 days at which time they will be asked to return for another in-person follow-up visit with the Site Study Coordinator. While it is extremely unlikely that any child's acute respiratory symptoms will persist this long, this process will be repeated until the child's acute respiratory symptoms resolve or they reach the end of follow-up at six months, whichever occurs first. We have chosen the number of days to

return to baseline respiratory symptoms as our primary outcome because persistent respiratory symptoms can have a major impact on a family's quality of life through missed sleep, school/day care, or work. Global assessment of respiratory symptoms by parents is often used as the primary outcome in this age of child because of the difficulties in obtaining more objective outcomes.

**Secondary Outcome:** - Secondary outcomes will be 1) the number of days children are given a SABA in the 21 days following study enrolment, and 2) the time to disease exacerbation at 6 months follow-up. The number of days children are given SABA has been chosen as one of two secondary outcomes because it is an objective measure of disease activity, and should parallel and compliment the primary outcome. Only children prescribed a SABA at the time of discharge from the ED will be included in the analysis of the secondary outcome. The other secondary outcome, disease exacerbation, will be defined as an unscheduled visit to a physician/nurse practitioner or treatment with an oral corticosteroid for acute symptoms of cough, wheeze, or respiratory distress (based on parental perception) that occurs after the child's initial symptoms have resolved. Primary care physician chart extraction at 6 month follow-up will be used to identify any reported unscheduled physician visits for respiratory symptoms. We have chosen time to disease exacerbation as a secondary outcome because it will capture another potential way in which azithromycin may benefit the patient. If a child has clinically occult sinusitis, then resolution of this infection could remove the trigger for a child's recurrent episodes and allow a longer period free of respiratory symptoms.

**Other Outcomes:** - Additional outcomes will be the number of physician visits, missed day care/school by children, and missed hours of work for wages by either or both of the parents (hours missed per day) due to their child having cough, wheeze, or difficulty breathing.

***Ethical considerations:*** Participation in this randomized placebo controlled clinical trial will involve nominal risk to the participants. There will be no significant inconvenience to families, no prolongation of their stay in the emergency department, no cost, and no significant pain, suffering, nor invasive tests. The study protocol will be reviewed and approved by the ethics review committee at each study site before the trial begins.

***Safety monitoring committee and termination policy:*** Adverse events will be actively monitored up to 30 days after the last of Azithromycin was given (day 5). Any child who develops symptoms consistent with adverse effects to azithromycin as evidenced by diarrhea or loose stools, nausea, abdominal pain, and vomiting (common side effects), symptoms of allergic reaction (hives), changes in mood or behaviour, arrhythmia/tachycardia will result in the review of their case by a safety monitoring committee consisting of a pediatric pulmonologist, allergist, and general pediatrician. The committee will review the case and decide whether to break the code and/or terminate the study based on the particulars of the case. If upon review there are concerns about the patient, the code would be broken and the randomization drug discontinued. The panel may consider terminating the study if there are profound adverse effects that would reflect concerns for all children.

***Sample Size and Minimal Clinically Important Difference:*** The telithromycin in acute adult asthma study demonstrated a 50% reduction in asthma symptoms among those using telithromycin (16% asthma symptoms in the placebo group versus 8% in the telithromycin group). We have used this data to estimate the magnitude of effect for our sample size calculations (a 50% decrease in the number of days to symptom resolution). Enrolment of 110 children per treatment arm per first-time versus previous wheeze (total 440), using a one-way ANOVA, will provide 80% power to detect at the .05 level, a 1.18 day

differences in the two treatment groups. This calculation assumes a conservative standard deviation of 6 days in symptoms duration and a 10% loss to follow-up. For the planned sub-group analysis of first-time versus previous wheeze, we have sufficient power to detect a 1.36 day difference between the azithromycin and placebo groups (*Appendix M – Power Calculation*). We think that a reduction in the duration of symptoms by one day or more is likely to be considered meaningful because of its implication for a child missing daycare or school, or parents missing work.

**Statistical Analysis:** The baseline variables in the two groups will be compared overall and by enrolment center in terms of means, standard deviation, and range, and as appropriate, median, inter-quartile range, percentages and 95% confidence intervals. Imbalances between treatment groups for key baseline variables such as age, gender, duration of illness, presence of atypical bacteria, use of ICS or oral corticosteroids, and baseline clinical severity will indicate the need for an adjusted analysis. We will also include an interaction term in the analysis (drug X presence or atypical bacterial infection) to determine if azithromycin has a different degree of effectiveness among those with atypical bacteria present. Furthermore, for each response variable, we will perform an exploratory adjusted analysis incorporating enrolment center as a factor to ensure that unmeasured differences between enrolment centers do not bias our results. The primary outcome, time to symptom resolution, will be assessed for normality of distribution by the Wilk Shapiro Test and, if necessary, will be transformed to yield suitable distributions or Kruskal Wallis (non parametric ANOVA analogue) will be used to test the main hypothesis. If the one way ANOVA is significant, then, a-priori decided comparisons (placebo versus azithromycin in first-time wheezing children and placebo versus azithromycin in children with a prior wheeze history) will be tested via Tukey's Honest significant differences procedure. If an adjusted analysis is necessary, we will use an Analysis of Covariance model incorporating those baseline factors which are imbalanced between treatment groups and any other variable that is thought to be of clinical relevance. An adjusted analysis will be performed in the event that co-intervention numbers (such as ICS or oral corticosteroid use) between the groups are not comparable. We also plan to perform a sub-group analysis to detect clinically significant differences in the each of the two wheezing sub-groups. Linear regression will be used to analyze  $\beta$ -agonist use during the 21 day follow-up period and Cox regression modelling will be used to analyse the time to next disease exacerbation.

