**Co-Interventions and Contamination:** Staff ED physicians will be asked not to treat enrolled patients with antibiotics. Otherwise physicians will be allowed to prescribe any treatment, in addition to the study drug and rescue SABA, they judge to be necessary (e.g. oral or inhaled corticosteroids). While treatment with corticosteroids has the potential to contaminate the effects of the study medication, given our study's randomized design, each treatment group will most likely have comparable numbers of patients treated with co-interventions. All medications (including duration and dosages) patients receive at enrolment and during follow-up will be documented. A letter will also be sent to the child's primary care physician at the time of enrolment detailing the nature of the study and that the child has been randomized to either azithromycin or placebo to be taken for 5 days in total.

**Data gathering and Patient Follow-up** (*Appendix H – Data quality & monitoring*)  
**Daily Symptom Diary:** Parents will be given a Ordinal Daily Symptom Diary with the following ordered categories: heart = 'no respiratory symptoms'; green star = 'mild respiratory symptoms'; yellow star = 'respiratory symptoms are worse than usual or more medication than usual was required'; red star = 'respiratory symptoms sufficiently severe to require an unscheduled visit to a physician or treatment with oral corticosteroids' or Blue star = in addition to one of the above and a cold or flu symptoms appear. Star stickers are to be provided to place in blue boxes each day of study syrup is provided. Parents will be

instructed to focus on any noisy breathing respiratory symptom (wheezing or whistling sounds), breathlessness with eating or speaking, shortness of breath after activity or exposure to cold, or persistent troublesome coughing. (*Appendix G – Ordinal Daily Symptom and Drug Dosing Diary*). This Ordinal Daily Symptom Dairy has been used in a prior study by PM with excellent parental and child compliance, and good discrimination in respiratory symptoms between treatment groups (Montelukast versus placebo).

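### The star colours in the primary outcome contradict the diary's codes: by colour, worse-than-usual (yellow) days count as resolved and symptom-free (heart) days are not listed

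*Protocol*

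**What the plan says.** Everything here is in section 6 (Research Design) of the protocol.

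- **Outcome Measurements, Primary Outcome.** Acute symptoms are resolved after "three consecutive days of their child having either no (*green star*) or usual (*yellow star*) respiratory symptoms". The paragraph refers to the diary in Appendix G. It gives the aim as the number of days to "return to baseline respiratory symptoms as our primary outcome because persistent respiratory symptoms can have a major impact".
- **Data gathering and Patient Follow-up, Daily Symptom Diary.** The ordered categories, again with reference to Appendix G, begin "heart = 'no respiratory symptoms'; green star = 'mild respiratory symptoms". Next comes "yellow star = 'respiratory symptoms are worse than usual or more medication than usual was required", and then "red star = 'respiratory symptoms sufficiently severe to require an unscheduled visit to a physician or treatment with oral corticosteroids". A blue star is recorded on top of one of these when cold or flu symptoms appear.
- **Outcome Measurements, Secondary Outcome.** An exacerbation counts only if it is one "that occurs after the child's initial symptoms have resolved".
- **Primary Outcome, extension rule.** A child not resolved at the day 21 visit receives another diary for a further 21 days. This repeats until resolution or six months.

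**The concern.** The data for the primary outcome are stickers. Parents place one each day, and the telephone follow-up asks about the previous day's stickers. Whoever scores the outcome therefore needs a rule that turns sticker codes into resolved or not resolved. The protocol gives one such rule, and neither of its two colour labels has the meaning that the diary paragraph gives it. Absence of symptoms is a heart in the diary, not green. Yellow is worse than the child's norm, not usual. The diary description has no category for usual at all.

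This is the trial's only primary outcome. The same date opens the period in which an exacerbation can count, and it decides which children go on to a second diary and a further visit. If the mapping stays open until data are in hand, the primary result depends on a choice made late.

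**Working it through.** The protocol gives no figure to reproduce on this point, so the check sets the two paragraphs side by side. The inputs are the diary categories (Daily Symptom Diary paragraph) and the resolution rule (Primary Outcome paragraph).

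| Diary code | Meaning in the diary paragraph | Resolved by the colours of the rule? | Resolved by the words of the rule (none or usual)? |
|---|---|---|---|
| Heart | none | not listed | yes |
| Green | mild | yes | only if mild means usual, which is not stated |
| Yellow | worse than usual, or extra medication | yes | no |
| Red | unscheduled visit or oral corticosteroids | no | no |

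1. Heart and yellow are classified in opposite ways by the two readings, green is unsettled, and red is the same in both. So 2 of 4 codes are reversed and 1 of 4 is undefined.
2. By colour, three yellow days in a row meet the event while the child is still worse than usual. By the words they do not.
3. By colour, three heart days in a row do not meet the event. Read literally, a child with hearts throughout never meets it and would be handed a further diary at day 21. By the words, that child is resolved from the first day.
4. The stated aim, return to baseline, agrees with the words and not with the colours.

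One assumed course shows how a single child's date moves. Take yellow on days 1 to 5, green on days 6 to 9 and hearts from day 10, and date the event at the first of the three qualifying days (a convention chosen for this illustration).

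- By colour: days 1, 2 and 3 are yellow, so the event is on **day 1**.
- By the words, with mild taken as usual: days 6, 7 and 8 are green, so the event is on **day 6**.
- By the words, with mild not taken as usual: days 10, 11 and 12 are hearts, so the event is on **day 10**.

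The course is invented. It shows only that the scoring rule decides the date.

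**The case against.** The best defence is that the intent is clear. The words admit children with no or usual symptoms, the aim is return to baseline, and a sensible analyst would follow the words. The colours may be left over from another version of the diary; the same paragraph calls the continuation diary nominal where the diary paragraph calls it ordinal. Appendix G is not shown, so what parents actually see is unknown. These points may explain the error and show which way to correct it. They do not remove it: the two paragraphs conflict in the current text and nothing in it says which governs. Nor is this a detail left to a statistical analysis plan, because the protocol fixes a definition and does so inconsistently.

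Four stronger readings are tempting, and the documents do not support them.

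- *Every child without a red day resolves on day 1.* Hearts are not in the colour rule, so this needs green or yellow on each of the first three days.
- *Between-child variation disappears.* Red and heart days would still separate children under the colour reading. Red includes oral corticosteroid treatment, which physicians may prescribe under Co-Interventions and Contamination.
- *The shift of 5 to 9 days in the illustration (6 − 1 and 10 − 1) dwarfs the 1.18-day target difference.* The first is one invented child scored under different rules; the second is a difference between arms. A shift common to both arms need not change that difference.
- *Counting symptomatic children as resolved is itself the fault.* The definition admits usual symptoms on purpose, which suits a return-to-baseline outcome. The fault is admitting days that are worse than usual or need extra medication.

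The blue star needs no repair for this point, since it is recorded in addition to a severity code.

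**Conclusion.** The definition of the sole primary outcome is wrong as written. Its colours contradict the diary's codes and its own words. Its size is categorical: two of the four severity codes are classified in opposite ways, and a third depends on an equivalence between mild and usual that the protocol never states. The error carries over to the start of the exacerbation outcome and to the day 21 extension rule.

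How many children would be misdated, and whether the treatment comparison would be biased or lose power, cannot be derived from the protocol, which gives no sticker frequencies. The conclusion rests on the diary paragraph describing the Appendix G diary correctly. If the printed form differs, the diary paragraph also needs correction, and the two paragraphs still have to be reconciled.

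**What to change.** Before unblinding, restate resolution in the diary's own codes and use the same mapping in the Daily Symptom Diary paragraph, the Primary Outcome paragraph and Appendix G:

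- heart days count as resolved;
- yellow and red days do not;
- green days count if the investigators confirm that mild covers the child's usual symptoms. This would fit the return-to-baseline aim, but it is their decision about the endpoint and should be written down.

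The exacerbation outcome and the day 21 extension rule then take the same resolution date without further change. The cost is a one-paragraph amendment and a check of the printed diary and the scoring program. No new data are needed.

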## 8. ANTICIPATED RESULTS, TIMELINES, and KNOWLEDGE TRANSLATION

This study provides us an opportunity to test the use of antibiotics in wheezing children; a treatment strategy frequently used by community physicians. A positive study will help us improve the management of this difficult to treat population. A negative study provides us an opportunity to educate community physicians on the lack of evidence for antibiotics in preschool children with wheeze.

Knowledge translation strategies, in addition to publication in peer-reviewed journals, will include incorporation of our findings into future versions of the Canadian Asthma Consensus Report, and an Alberta provincial clinical pathway for children with asthma. (Note these initiatives incorporate preschool children into their recommendations.) Incorporation of this evidence is assured as [name] is a long-serving member of the Canadian Asthma Consensus working group and [name] co-chairs and Drs. [name] and [name] are members of the Alberta Health Services (AHS) committee charged with developing and implementing a provincial childhood asthma pathway. The planned implementation strategy for the AHS pathway initiative is to develop a highly interactive web-curriculum module designed for primary care practitioners, and disseminate it through the 95 Alberta hospitals and 30 primary care networks to physicians, nurses, and respiratory therapists who care for Albertan children with asthma.

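### The sample-size paragraph cites a halving of symptom days but calculates on 1.18 days with nothing linking the two, and its own inputs give about 50% power at 1.18 days and 38% at the one day it calls meaningful

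*Protocol*

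**What the plan says.** The paragraph on sample size and minimal clinically important difference (Protocol, section 6) makes these statements in turn.

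- **Source of the effect.** "The telithromycin in acute adult asthma study", reported as "16% asthma symptoms in the placebo group versus 8% in the telithromycin group".
- **Transfer to this trial.** The halving is applied to time to resolution: "We have used this data to estimate the magnitude of effect for our sample size calculations (a 50% decrease in the number of days to".
- **Calculation.** "Enrolment of 110 children per treatment arm per first-time versus previous wheeze (total 440), using a one-way ANOVA", which "will provide 80% power to detect at the .05 level, a 1.18 day" difference between treatments. The inputs are an SD of 6 days, described as conservative, and 10% loss to follow-up. For each wheeze-history subgroup, sufficient power is claimed for 1.36 days, with a reference to Appendix M.
- **Meaningful difference.** "We think that a reduction in the duration of symptoms by one day or more is likely to be considered meaningful".

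Two other places bear on this. In section 6, Outcome Measurements, resolution is "defined as three consecutive days of their child having either no" or usual symptoms. Section 8 says: "A negative study provides us an opportunity to educate community physicians on the lack of evidence for antibiotics in preschool children with wheeze".

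**The concern.** The paragraph offers three effect sizes: a 50% reduction, 1.18 days and one day. The first is a relative change in a symptom measure from adults on another drug, relabelled as a relative change in days for preschool children. A percentage becomes a number of days only through a placebo mean in days, and the text at hand gives none. A reader cannot tell how the 50% figure entered the calculation, if it did.

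At stake is how a null result will be read. Section 8 already plans to take a negative trial to community physicians. That is sound only if the trial is precise enough to exclude the benefit that the protocol itself calls meaningful. The stated 80% power at 1.18 days suggests that it is, so the statement has to be checked against the SD and sample size given beside it.

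**Working it through.** **Inputs (Protocol, section 6, sample-size paragraph).** 110 per arm per stratum, so 220 per arm and 440 in total; 10% loss, leaving 220 × 0.9 = 198 per arm, or 99 per arm within a stratum; SD 6 days; alpha 0.05. Sidedness is not stated; two-sided is assumed. Normal approximation for a difference in means.

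**1. The plan's own figure.** SE = SD × √(2/n).
- n = 198: SE = 6 × √(2/198) = 0.603. Then 1.18/0.603 = 1.957, and power = Φ(1.957 − 1.960) ≈ 50%.
- n = 220 (no loss): SE = 0.572; power ≈ 54%.
- One-sided: 62% (198) or 66% (220).
- One-way ANOVA across the four treatment-by-stratum cells, with the same 1.18-day effect in both strata: 34% (99 per cell) or 38% (110 per cell).

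None of these gives 80%. Reaching 80% at 1.18 days would need an SD of about 4.2 (198 per arm) or 4.4 (220 per arm). At SD 6 it would need 406 evaluable per arm; 406/0.9 gives 452 per arm, or 904 children in total.

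**2. What the inputs deliver.** Difference detectable with 80% power = (1.960 + 0.842) × SE.

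| Comparison | n per arm | Detectable at 80% | Plan states |
|---|---|---|---|
| Overall | 198 | 1.69 d | 1.18 d |
| Overall, no loss | 220 | 1.60 d | 1.18 d |
| Within stratum | 99 | 2.39 d | 1.36 d |
| Within stratum, no loss | 110 | 2.27 d | 1.36 d |

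The two stated figures also disagree with each other. Halving n should multiply the detectable difference by √2 = 1.41, but 1.36/1.18 = 1.15.

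**3. The one-day difference.** 1.00/0.603 = 1.658; power = Φ(1.658 − 1.960) ≈ 38% (about 42% with no loss).

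**4. Precision.** 95% half-width = 1.96 × 0.603 = 1.18 days (1.12 with no loss). An observed difference of zero gives an interval of about −1.18 to +1.18 days, which contains a one-day reduction. To exclude it, the observed result would have to favour placebo by more than 1.18 − 1.00 = 0.18 days.

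**5. Linking 50% to days.** If 1.18 days is a 50% reduction, the placebo mean is 1.18/0.50 = 2.36 days and the azithromycin mean is 1.18 days. If 1.36 days is a 50% reduction within each stratum, the placebo mean is 2.72 days in both, so the pooled mean would be 2.72 days, not 2.36. A mean of 2.36 days sits awkwardly with an SD about 2.5 times as large (6/2.36) and with a criterion of three consecutive days.

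**6. Power for a halving.** The placebo means below are assumed, since the text gives none; SD 6, 198 per arm.

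| Placebo mean | 50% reduction | Power |
|---|---|---|
| 2.36 d | 1.18 d | 50% |
| 3 d | 1.5 d | 70% |
| 4 d | 2.0 d | 91% |
| 6 d | 3.0 d | over 99% |

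**The case against.** **A longer placebo mean helps the trial.** If children take longer than 2.36 days to resolve, a halving exceeds 1.18 days and is better powered. This stands. A reader might infer that the trial is underpowered for a 50% effect, or that the 50% effect is not the one tested. The documents support neither: 1.18 days can be read as a detectable difference lying near the one-day threshold.

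**The adult 16% is not a control value in the calculation.** Correct. No control mean visibly enters the calculation in days, so it would be wrong to say that the trial borrowed its control rate from adults. The fault is that the link is missing.

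**Appendix M is cited but not at hand.** It may contain a placebo mean. It could not make 80% power, 1.18 days, SD 6 and 440 children agree under the calculations above, nor make 1.18 and 1.36 days both halves of a common mean.

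**The harm comes from n and SD, not from the 50% statement.** True. If 80% power at 1.18 days held, the SE would be 1.18/2.80 = 0.421 and the half-width 0.83 days; an observed zero would then exclude a one-day benefit. So the power statement has to be corrected together with the rationale.

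**SD 6 is called conservative.** A smaller SD would help: with 198 per arm the half-width falls below one day once the SD is under about 5.1 (1/(1.96 × √(2/198))). The plan gives no such SD.

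**The three-day criterion and the day-21 visit do not fix a mean.** Agreed. The protocol does not say whether time runs to the first or the third qualifying day, and follow-up continues past day 21 for unresolved children. They make 2.36 days look short; they do not rule it out.

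**Section 8 speaks of lack of evidence, not of proven absence of benefit.** That is so, and it should not be read as a claim of equivalence. It still sets no condition on precision before the message goes out.

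**Conclusion.** The point holds in this form. The paragraph presents a 50% decrease as the basis of the sample size, states the result as 1.18 days, and in the text at hand has nothing to connect them; agreement requires a placebo mean of 2.36 days (2.72 for the subgroup figure). On its own this is a gap in the rationale.

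The consequence comes from the plan's own inputs. Power is about 50% at 1.18 days, not 80%, and 38% at one day. The difference detectable with 80% power is about 1.7 days overall (1.6 with no loss) and about 2.4 days within a stratum. The 95% interval extends about 1.18 days either side, so a null result centred on zero could not exclude the benefit that the protocol calls meaningful.

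These figures assume SD 6, 198 evaluable per arm, a two-sided 0.05 test and a comparison of means. A transformation or rank test, which the protocol allows, would change them somewhat. The change should be made, but it concerns what is stated and concluded, not the conduct of the trial.

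**What to change.** **Section 6, sample-size paragraph.**
- Stop presenting the adult 50% figure as the basis of the calculation, or give the placebo mean in days for this population, with its source, that links it to the design difference.
- State one design difference in days.
- Replace the claim of 80% power at 1.18 days with what 440 children, SD 6 and 10% loss deliver: about 1.7 days at 80% power, 38% power at one day, and a 95% interval of about ±1.2 days. Make these changes together; adding the 38% beside the existing 80% claim would create a new contradiction.
- Recompute the 1.36-day subgroup figure on the same basis: about 2.4 days at 80% power with 99 per arm.
- State the sidedness of the test, and bring Appendix M into line.

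**Section 8.** Have a non-significant result reported with its 95% confidence interval in days. Conclude that a meaningful benefit is absent only if the interval excludes a one-day reduction; otherwise call the result inconclusive.

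**Cost.** Wording only, with no extra children or data. The stated power becomes less favourable, and a null result may have to be reported as inconclusive.
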